### Eligibility criteria

#### Inclusion criteria

Patients will be eligible for inclusion if they are consistent will all of the following criteria: (1) adult patients (50–75 years of age) with significant knee pain (defined as pain score ≥ 40 mm on the 100mmVAS scale), (2) having a diagnosis of knee osteoarthritis per the diagnostic criteria of the American College of Rheumatology (ACR) and the Chinese Orthopedic Association, and (3) having a radiographic Kellgren-Lawrence grade I or II knee OA and MRI findings of bone marrow edema-like lesions. The inclusion of bone marrow edema-like lesions (identified by high bone turnover through MRI) is because they are associated with greater response to bisphosphonates [19].

#### Exclusion criteria

Patients will be excluded if they have one of the following criteria: (1) having any forms of active arthritis (such as rheumatoid arthritis or other inflammatory arthritis), (2) users of non-steroidal anti-inflammatory drugs (NSAIDs) and central analgesics (such as opioids) within two weeks or other study drug or device within 30 days before randomization or within the drug half-life (whichever is longer), (3) evidence of abnormal liver function tests (ALT or AST; at least a 1.5-fold increase above the upper limit of normal), (4) having renal dysfunction, osteomalacia, or creatinine clearance < 35 mL/min, (5) having serious heart disease, endocrine, digestive, mental, nervous system diseases, cancer, or serious illnesses with a life expectancy of less than two years, (6) pregnancy or breast-feeding, (7) having active ulcers, history of upper gastrointestinal bleeding, or esophageal motility disorders, (8) having fracture within 6 months of study initiation, (9) tobacco addiction or alcohol abuse, (10) having allergy or contraindication to study medications, (11) contraindications to MRI or X-rays exposure, (12) planned joint replacement within the study period, or (13) having poor dental health or scheduled dental surgery before or during the study period.

### Patient recruitment

According to the principle of fair distribution of burden and benefit, relevant information will be released through a participant recruitment announcement → prospective participants will read the study introduction → informed consent will be obtained from eligible individuals → selected participants will then undergo randomization to receive the treatment or placebo.

### Randomization and blinding

Randomization will be performed using a variable-sized block (sizes of 4, 8, and 12), computer-generated randomization procedure to ensure equal number of participants within each treatment arm. The execution of block randomization will be done by the SAS software, where a different block will be implemented each time the value within the parenthesis of the ranuni function of the macro set reaches zero. The assignments will be blinded to both the investigators and study participants and concealed within sealed, fully opaque envelops. Of note, emergency unblinding will only be allowed in critical situations where the safety of included participants is affected.

Allocation concealment will be ensured with the use of sequentially numbered, opaque, sealed envelopes within containers. There will be a coordinating center for this particular step and a particular study personnel will carry out the allocation of patients.

### Outcome measures

#### Primary outcome

Our primary outcome is to determine the improvement in knee structure following each intervention using an MRI-based scale named the Whole-Organ Magnetic Resonance Imaging Score (WORMS) scale at 6 and 12 months after treatment allocation [20]. The WORMS scale is designed to determine the status of the knee joint in patients with OA in respect to fourteen independent articular features. Five out of the 14 features are related to the articular surfaces, and they include: (1) cartilage signal and morphology, (2) subarticular bone marrow abnormality, (3) subarticular cysts, (4) subarticular bone attrition, and (5) marginal osteophytes. In addition, all of these features are further evaluated in 15 different regions divided by anatomical landmarks in a fully-extended knee (Supplementary Fig. 1). For the purposes of our research, we will focus on cartilage signal and morphology. This feature is scored based on only 14 articular surface regions (excluding region S), with a score ranging from 0 to 6 on an 8-point scale (Supplementary Fig. 2). The WORMS scoring system for cartilage includes 0 = normal cartilage thickness and signal, 1 = normal cartilage thickness but with increased signal, 2 = a partial-thickness defect of < 1 cm in the greatest width, 2.5 = a full-thickness focal defect of < 1 cm in the greatest width, 3 = multiple regions having partial-thickness defects alternating with regions of normal thickness or defects > 1 cm, 4 = diffuse partial-thickness defects, 5 = multiple regions of full-thickness defects or defects > 1 cm, and 6 = diffuse full-thickness defects, with an overall score ranging from 0 to 84.

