**Methods:**

This multicenter, randomized, double-blinded, placebo-controlled study will evaluate the efficacy and safety of alendronate in early OA. Patients will undergo a 1:1 double-blinded randomization to receive a one-year course of either alendronate sodium vitamin D_3_ or placebo. The primary outcome is to compare WORMS score of knee joint at 6 and 12 months between both groups. Secondary endpoints will include WORMS score at 24 months, knee pain, radiographic progression of OA, severity of OA, quality of life, and serum inflammatory biomarkers at different assessment timepoints. To detect a 2.2% difference in cartilage loss between both groups with power of 80%, a sample size of 60 (30 per group) is proposed.

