### Trial objectives

This designed randomized controlled trial will explore the efficacy of alendronate sodium vitamin D_3_ compared to placebo on the improvement of joint structure and pain in patients with knee osteoarthritis. Our primary hypothesis is that there will be a significant improvement in the joint structure, as measured by the WORMS scale, in favor of alendronate at each assessment timepoint. Our secondary hypothesis is that there will be a significant improvement in knee pain, severity of OA, and quality of life, as well as a significant reduction in the level of inflammatory biomarkers, among patients assigned to the alendronate sodium vitamin D3 as compared to those given placebo.

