### Sample size calculation

Based on a previous observation, the mean annual loss of the medial tibial cartilage volumes in knee OA patients is 4.5% [25]. The monthly intake of vitamin D (50,000 IU) would result in a serum vitamin D3 level > 60 nmol/L [26], and this, in turn, has been reported to correlate with a 2.2% annual absolute reduction in cartilage loss [27]. This can be translated into a risk reduction of 22% for knee replacement over a period of 2 years [28]. Our sample size calculation was conducted based on Cohen’s formula [29]. With a power level of 80% and alpha level of 0.05, 60 participants (30 in each group) were required to detect a 2.2% between-group difference in terms of medial tibial cartilage loss (WORMS scale) during the second assessment time-point (12 months). Losses to follow-up were not considered in our initial sample size calculation (*NCT04739592*); however, given the fact that both interventions will be administered for a year and patients will be followed up for 2 years after enrollment, we anticipate that around 10% will be lost to follow-up each year, so we increased our final sample size to 220 participants (110 in each group).

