### Statistical analysis

Retrieved data from each patient in both groups will be recorded at baseline and at each follow-up assessment period using Excel, which will then be entered into a software for analysis after the final assessment point has been met. All statistical analysis will be conducted by a third-party (not involved with our research in any way) using the Statistical Analysis System (SAS) Software for Windows (version 9.4, *SAS institute, USA*).

Baseline demographic and clinical variables will be presented in the form of number and percentages for categorical variables, while continuous variables will be presented as means and standard deviations (SD) or median and range if the data were normal or skewed, respectively.

Our primary outcome will be analyzed with the intention-to-treat (ITT) analysis and reported as the mean difference (MD) and corresponding 95% confidence interval (CI) in cartilage-WORMS score between the intervention and control groups using Student’s t-test. Secondary outcomes will then be analyzed at the final assessment. Pain will be analyzed as a categorical outcome using the chi-square test, while the differences in continuous determinants of pain (baseline variables) will analyzed using MANOVA test. The QoL will be analyzed and reported as the mean difference and its corresponding 95% CI between both interventions using t-test. Bone density and osteoporosis severity (measured by the Kellgren-Lawrence scale) will be analyzed as categorical outcomes (normal, low density, osteoporosis) using the Chi-square test. Meanwhile, differences in serum levels of inflammatory biomarkers between both groups will be measured using t-test. In order to account for missing data, survival analyses will be conducted while implementing the “last-observation carried forward” approach. Such data will be presented in Kaplan–Meier curves, showing the numbers of patients analyzed at each assessment timepoint. A *p*-value of less than 0.05 will indicate statistical significance.

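### The primary outcome names cartilage WORMS at 6 and at 12 months without ranking them or fixing a both/either rule, while the sample size covers 12 months only

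*Protocol article*

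**What the plan says.** Five places in the protocol article bear on the decision rule.

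- Primary outcome: knee structure on the "Whole-Organ Magnetic Resonance Imaging Score (WORMS) scale at 6 and 12 months after treatment allocation", narrowed in the same section to cartilage signal and morphology. The abstract agrees: "The primary outcome is to compare WORMS score of knee joint at 6 and 12 months between both groups". Neither gives one time precedence.
- Trial objectives: the primary hypothesis is a significant improvement in joint structure "as measured by the WORMS scale, in favor of alendronate at each assessment timepoint".
- Secondary outcomes: WORMS at 24 months is listed here, not as primary.
- Sample size calculation: "With a power level of 80% and alpha level of 0.05, 60 participants (30 in each group) were required" to detect a 2.2% difference "during the second assessment time-point (12 months"). The same paragraph then expects about 10% loss per year and raises the total to 220 (110 per group). It restates no power at 220 and gives no SD.
- Statistical analysis: the primary outcome is the mean difference "in cartilage-WORMS score between the intervention and control groups" with a 95% confidence interval, by Student's t-test under intention to treat. No timepoint, order or adjustment is attached. The only threshold is that a *p*-"value of less than 0.05 will indicate statistical significance".

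**The concern.** With two primary timepoints, the type I error and power depend on what counts as success, and the document does not settle that. The outcome definition lists two times side by side, the hypothesis says each, and the sample size treats 12 months as the one that matters. A result significant at 6 months but not at 12, or the reverse, could be called a success or a failure after unblinding, with wording in the protocol to support either. This affects the trial's main conclusion.

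Silence about multiplicity could be left to an analysis plan that is not shown. Here, though, the protocol itself states an unranked pair, a hypothesis worded as each, and a calculation for one of the two. An analysis plan that put 12 months first would still leave the abstract, the objectives and the outcome definition needing amendment.

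**Working it through.** **Inputs from the document.** Alpha 0.05 (sidedness not stated; two-sided assumed), power 80%, 30 per group, difference 2.2 percentage points at 12 months, loss about 10% per year, final 110 per group, 1:1 allocation.

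**Inputs assumed.** The correlation ρ between the 6- and 12-month test statistics is not given, so 0.5 to 0.9 is shown. The size of the 6-month effect is not given, so a range is shown.

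**Step 1: the plan's own figure.** Without an SD, the 30 per group cannot be reproduced, only inverted. The standardised effect is d = (1.960 + 0.842) / √(30/2) = 0.723, so SD = 2.2 / 0.723 = 3.04 points (2.99 with the noncentral t). Put forward again, SD 3.0 returns 30 per group. The later steps use d = 0.723.

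**Step 2: success at either time.** The type I error is 1 − P(|Z₆| < 1.96 and |Z₁₂| < 1.96), with Z₆ and Z₁₂ standard bivariate normal with correlation ρ.

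| ρ | Type I error |
|---|---|
| 0 (independence) | 9.75% |
| 0.5 | 9.1% |
| 0.7 | 8.3% |
| 0.8 | 7.8% |
| 0.9 | 7.0% |

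These do not depend on the sample size, so going from 60 to 220 does not change them.

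**Step 3: success at both times.** The type I error cannot exceed that of one test, so it is at most 5%. Joint power is P(Z₆ > 1.96 and Z₁₂ > 1.96), with means m₁₂ = d√(n/2) and m₆ = f·m₁₂, where n is the number per group and f is the standardised 6-month effect as a fraction of the 12-month one.

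The final 110 per group leaves 110 × 0.90 = 99 after one year's loss, or 110 × 0.81 ≈ 89 after two. The means m₁₂ are 2.80 at n = 30, 4.82 at n = 89 and 5.09 at n = 99.

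| n per group | f = 1 | f = 0.71 | f = 0.5 |
|---|---|---|---|
| 30 (stated calculation) | 69–75% | 46–51% | 27–29% |
| 89–99 (final 220 after loss) | over 99% | 93–95% | 67–72% |

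At n = 30 the range reflects ρ from 0.5 to 0.9. At n = 89–99 it reflects n, because ρ then hardly matters.

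**Where the values of f come from.** The sample size section reasons in annual rates. A steady rate would give about half the difference at 6 months, so f = 0.5 if the SD is the same at both times. If instead the variance of change grows in proportion to time, the 6-month SD is about 0.71 of the 12-month one, and f = 0.5 / 0.71 ≈ 0.71. The document supports neither case over the other. Its annual figures are also cartilage volume loss, not WORMS points.

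**The case against.** The strongest reply is that the only wording about success, "in favor of alendronate at each assessment timepoint", points to requiring both times, and nowhere does the document say that one is enough. On that reading the type I error is controlled. This stands: the 7.0 to 9.1% applies only if a single-timepoint win may be claimed, which the text fails to exclude but does not assert. Testing each time at 0.05 is likewise the plain reading of a general threshold, not an explicit sentence.

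A reader might go further in three ways that the documents do not support.

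- That the stated error rates fail under every reading. Requiring both times keeps alpha at or below 0.05. At 220 with equal effects, joint power is above 80% as well.
- That the planned trial has joint power of only 27 to 29%. That figure belongs to 30 per group with a halved standardised 6-month effect. The sample size section ends at 220, where the same scenario gives 67 to 72%.
- That each timepoint takes in 24 months. The outcome sections confine the primary outcome to 6 and 12 months and list 24 months as secondary.

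It can also be said that an unseen analysis plan may set the order of testing. It may, but it could not make the three protocol statements agree as they are written.

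**Conclusion.** The concern holds as a decision rule left open: two unranked primary timepoints, only one of them sized. What remains unsettled is the basis on which the trial would claim success.

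Its size depends on the rule eventually applied. Under an either-time rule, the inflation from 5% to 7.0–9.1% rests only on the assumed correlation. Under a both-times rule there is no inflation, and the cost is in power. At the 60 to which the 80% is attached, joint power falls short of it even with equal effects. At 220 the shortfall appears only if the standardised 6-month effect is well below the 12-month one. The power figures at 220 rest on an SD that the document does not state, on 10 to 19% loss, and on an assumed time course.

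Because the ambiguity touches the main conclusion and is cheap to remove, it should be resolved before unblinding.

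**What to change.** Name cartilage WORMS at 12 months as the single primary endpoint, tested at two-sided 0.05. It is the end of the one-year treatment course and the only time for which a sample size is given. Make 6 months secondary alongside 24 months, and test the two in a stated fixed sequence only if 12 months is significant. Bring the abstract, the trial objectives and the primary outcome section into line, and carry the same wording into the registry entry and any analysis plan.

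The planned t-test can stay; this repair does not need a repeated-measures model. No patients, visits or scans are added. The one loss is that an effect seen only at 6 months can no longer count as primary success.

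If the sponsor does want both times to be primary, the alternative is to state that both are required and to justify the joint power at 220 with an explicit SD and 6-month effect.

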#### Secondary outcomes

We have seven pre-identified secondary outcomes: WORMS score (at 24 months), pain intensity (at 2, 4, 8, and 12 weeks after enrollment), quality of life (QOL), bone density, risk of knee replacement, severity of knee OA, and estimation of inflammatory biomarkers.The structure of knee joint will be measured using the WORMS scale at 24 months after treatment.Knee pain will be measured in both groups at 2, 4, 8, and 12 weeks after enrollment using the 100-mm visual analogue scale (VAS), which has already been shown to be valid and reliable in measuring pain [21]. Overall ratings range from 0 to 100 mm, where 0–4 mm indicate no pain, 5–44 mm indicate mild pain, 45–74 mm indicate moderate pain, and 75–100 mm indicate severe pain.Quality of life in both groups will be assessed at 3, 6, and 12 months after enrollment using the previously validated Chinese version of the SF-36 questionnaire [22], which is used to measure health status based on eight categories: (1) physical activity, (2) social activity, (3) physical role, (4) energy and emotional status, (5) mental health, (6) vitality, (7) body pain, and (8) general health. The overall score ranges from 0–100, with higher scores reflecting better health-related QoL [23]. This version of the SF-36 questionnaire shows comparable validity and reliability to the original version.Bone density of the lumbar spine and the hip and knee joints will be carried out using dual-energy x-ray absorptiometry (DXA) at 12 and 24 months after enrollment. Bone density data will be obtained using a Prodigy DXA scanner (GE Healthcare, Madison, USA) and the obtained data will be analyzed according to the manufacturer’s software. The lumbar spine (L1-L4) and the hip (particularly the femur neck and total hip) will be scanned in the supine position using posteroanterior projections.The risk of knee replacement will be evaluated based on a set of baseline and clinical variables and then incorporated into a multivariable logistic regression model to identify significant predictors of knee replacement in patients with OA.Severity of OA will be measured at 12 and 24 months after enrollment using the Kellgren-Lawrence grading scale [24]. The scores of this grading scale range 0 to 4, where 0 indicates no features of OA, 1 indicates questionable osteophytes, 2 indicates definite osteophytes without narrowing in the joint space, 3 indicates definite osteophytes with moderate narrowing, and 4 indicates definite osteophytes with severe narrowing.The serum level of the following inflammatory biomarkers will be measured at 3, 6, and 12 months after enrollment: interleukin (IL)-6, tumor necrotic factor (TNF)-alpha, erythrocyte sedimentation rate (ESR), and C-reactive protein (CRP).

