**Discussion:**

This trial will give helpful and high-quality evidence regarding the potential therapeutic role of alendronate sodium vitamin D3, as compared to placebo, in the management of patients with knee OA regarding its role on cartilage loss, radiographic progression of OA, severity of OA, knee pain, quality of life, and inflammatory biomarkers. If proven effective, this intervention would be a great option for providing beneficial outcomes with a reduced cost in this patient population.

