High-quality evidence, limited to a few well-conducted randomized trials, highlights contradictory results on the effect of bisphosphonates (of different doses and administration routes) on knee function and disease progression in patients with knee OA [15–17]. Furthermore, another ongoing multicenter, randomized, double-blinded, placebo-controlled trial will compare the efficacy of annual infusions of zoledronate to placebo in terms of knee joint structural changes and knee pain in patients with knee OA [18]; however, the results are expected in 2022–2023. Therefore, and based on the above-mentioned observations, we are willing to conduct this randomized, placebo-controlled trial to determine the effect of combined alendronate sodium with vit D on the knee joint structure, knee pain, radiographic grade of OA, quality of life (QOL), and severity of OA in patients with knee OA and MRI evidence of bone marrow edema-like lesions since they show greater response to bisphosphonates [19].

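### Radiographic progression is named as a secondary endpoint in the abstract but is neither listed among the outcomes nor analysed, and the planned Kellgren-Lawrence test does not use the baseline grade

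*Protocol article*

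**What the plan says.** The Methods paragraph of the abstract includes among the secondary endpoints "radiographic progression of OA, severity of OA, quality of life, and serum inflammatory biomarkers at different assessment timepoints". Its Discussion paragraph says the trial will give evidence on "cartilage loss, radiographic progression of OA, severity of OA, knee pain, quality of life, and inflammatory biomarkers". Both list progression and severity as two items.

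The Secondary outcomes section announces seven pre-identified outcomes. After WORMS at 24 months, pain and quality of life, the list closes with "bone density, risk of knee replacement, severity of knee OA, and estimation of inflammatory biomarkers". Severity is then defined as the KL grade, read at 12 and 24 months. Progression has no entry.

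Under Inclusion criteria, every participant has KL grade I or II at entry. Statistical analysis places the secondary outcomes at the final assessment. It handles bone density and the KL measure in one sentence, with a chi-square test. There the KL measure is described as severity of osteoporosis, and the categories given are normal, low density and osteoporosis.

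**The concern.** A reader of the abstract expects a result on radiographic progression as well as one on severity. The section that fixes the outcomes supplies only severity, and the analysis section supplies only a comparison at one time point. If the plan is followed literally, the trial reports nothing on an endpoint that its abstract names twice. Whether the KL result is reported as final grade or as change from entry also stays open until the data are in, and the two can differ noticeably in how likely they are to show an effect.

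The mislabelled categories compound this. KL grades cannot be sorted into bone-density classes, so the severity analysis cannot be run as stated either.

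**Working it through.** **Step 1: compare the lists.** The abstract names six secondary endpoints and the Secondary outcomes section names seven.

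| Endpoint | Abstract | Secondary outcomes |
|---|---|---|
| WORMS at 24 months | yes | yes |
| Knee pain | yes | yes |
| Radiographic progression | yes | no |
| Severity of OA | yes | yes (KL grade) |
| Quality of life | yes | yes |
| Inflammatory biomarkers | yes | yes |
| Bone density | no | yes |
| Risk of knee replacement | no | yes |

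Five items are shared, one is in the abstract only (6 − 5), and two are in the outcomes section only (7 − 5).

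**Step 2: what data will exist.** KL grade is known at entry (eligibility) and read at 12 and 24 months. Change from entry is therefore available for every patient with a follow-up film. A follow-up grade of 3 or 4 is progression whatever the entry grade. Only a move from I to II needs the entry grade to be recognised, and the planned test does not use it.

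**Step 3: what a final-grade comparison does.** Let s be the share entering at KL I, let p be the probability of progressing, and let a progressor gain one grade. The final distribution is

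- grade 1: s(1 − p)
- grade 2: sp + (1 − s)(1 − p)
- grade 3: (1 − s)p

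The mean final grade is 2 − s + p. Randomisation makes s equal in expectation across arms, so the expected difference in means is the difference in p. The comparison is unbiased.

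The cost is in precision. Take s = 0.5, with p = 0.30 on placebo and 0.15 on active treatment. Grades 1, 2 and 3 are then 35%, 50%, 15% on placebo and 42.5%, 50%, 7.5% on active. Grade 2 is identical in the two arms. On placebo its 50% is made up of 15% who progressed and 35% who were stable.

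**Step 4: size of the loss.** None of these rates or splits is in the document; all are assumptions. Simulated power of a Pearson chi-square, two-sided 0.05, 110 per arm, 30% versus 15% progression:

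| KL I at entry | Final grade | Progressed yes/no |
|---|---|---|
| 10% | 61% | about 77% |
| 30% | 48% | about 77% |
| 50% | 37% | about 77% |
| 70% | 34% | about 77% |
| 90% | 49% | about 77% |

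If all patients enter at one grade, the two tests coincide and the gap disappears. With 10% lost per year, 110 × 0.9 × 0.9 ≈ 89 per arm remain at 24 months; at a 50% split, power is about 31% versus 67%. Also at a 50% split with 110 per arm, 25% versus 12% progression gives about 33% versus 71%, and 40% versus 20% gives about 53% versus 90%.

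**The case against.** The strongest reply is that this is a loose phrase in an abstract. The body of the article is more consistent. The Background speaks of "the knee joint structure, knee pain, radiographic grade of OA, quality of life (QOL), and severity of OA", where grade fits the KL scale and no progression is promised. The secondary hypothesis in Trial objectives expects "a significant improvement in knee pain, severity of OA, and quality of life" and leaves progression out. The main Discussion mentions progression only when describing a gap in the evidence. How a derived variable is defined is often left to a full protocol or analysis plan, and neither is shown. The trial is sized on cartilage loss, so power on a secondary radiographic measure was never claimed. The power figures rest on invented rates. The bone-density categories may also have been meant only for the bone-density half of the sentence.

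Much of this stands. Progression is a named trial endpoint only in the abstract, and the power figures are illustrative. A reader might infer that the final-grade comparison is invalid because a KL 2 patient could be either stable or progressed. That does not follow: randomisation balances entry grade in expectation, and the test is only less efficient.

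Two things remain. An unseen analysis plan cannot change the fact that the published article gives two different endpoint sets. And the article does fix an analysis for the KL measure, one that ignores the entry grade and carries a label and categories from another outcome. If those categories were meant for bone density alone, the sentence still needs repair, because it then states no KL categories.

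**Conclusion.** The point holds as an inconsistency with a modest analytic cost. The abstract names radiographic progression separately from severity, the list of seven outcomes omits it, and the analysis section neither defines nor estimates it.

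A reader might go further and conclude that the trial cannot deliver a progression result, or that its radiographic data are only cross-sectional. The document does not support that: the KL grade is read at entry and at 12 and 24 months, so progression is derivable from planned data.

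The loss from ignoring the entry grade is power, not validity. It is about 34% to 61% against about 77% for KL I shares of 10% to 90%, on the assumed 30% versus 15% one-grade progression with 110 per arm. The final-grade test was weaker in every mixed-entry scenario examined, but the size of the gap depends on an entry split and on rates that the document does not give. Since this is a secondary outcome and the remedy is cheap, it should be corrected, but it does not threaten the trial's main result.

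**What to change.** 1. Make the endpoint lists in the abstract (Methods and Discussion paragraphs) and in Secondary outcomes agree, including bone density and risk of knee replacement.
2. If progression is wanted, define it in Secondary outcomes against the patient's own entry grade. One option is the proportion with an increase of at least one KL grade at 12 and 24 months, reported by arm with risk difference and 95% CI. Another is an ordinal model of KL grade adjusted for entry grade. Choose one before unblinding.
3. If progression is not wanted, delete it from the abstract. That also reconciles the lists.
4. In either case, correct Statistical analysis so that the KL outcome is called osteoarthritis severity and uses KL grades, and keep the bone-density categories for bone density.

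The cost is wording plus, at most, one further analysis of data already planned; no new films are needed. A binary progression endpoint ignores changes of more than one grade, which the ordinal model would retain.
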